### Study Endpoints

In this study, the primary endpoint will be the OS. The secondary endpoints PFS and total complication rate. The total complications will include postoperative and chemotherapy complications. Postoperative complications were defined as events occurring within 30 days after the procedure, the severity of which was assessed by the ClavienDindo classification system (23, 24). Postoperative complications will include surgical site infection (SSI refers to the infection that occurs in the incision, deep organ or cavity during the perioperative period. It is mainly divided into superficial wound tissue infection, deep wound tissue infection and organ/cavity infection); anastomotic leaks and duodenal blow-out (identified clinically or radiographically); Chylous fistula (defined as milky white liquid in peritoneal drainage fluid after the start of enteral nutrition); respiratory complications (defined as clinical manifestation of pneumonia or bronchopneumonia confirmed by computed tomographic scan); and other complications (such as: delayedgastricemptying, intestinal obstruction, anastomotic and/or abdominal bleeding, abdominal abscess, pancreatic fistula, pancreatitis and so on.). Postoperative mortality was defined as all-cause death occurring within 30 days after the procedure. Chemotherapy complications refer to the side effects of chemotherapy, such as ototoxicity and nephrotoxicity. For those patients delayed postoperative systemic radiotherapy and/or chemotherapy after 4 weeks of surgery due to surgery and its complications, their clinical data were recorded in detail and analyzed by subgroup stratification.

Adverse events are adverse medical events that occur after surgical and medical treatment in patients in clinical trials. Adverse events, whether treatment-related or not, will be considered from the date participants sign informed consent until 5 years after the end of treatment in this study. The nature and severity of adverse events will be assessed in accordance with “expert consensus on diagnostic criteria for postoperative complications of gastrointestinal cancer in China”. The investigator will determine if the adverse event is clinically significant, and if so, it will be identified as an adverse event. The investigators will assess possible relationships among the adverse events, the investigational drugs and the surgery to assess adverse events and their causal relationship to treatment. Adverse reactions include those results recorded as positive, correlated, and possibly correlated. The investigators will keep a full record of serious adverse events from the start of the surgery to the end of the study. All serious adverse events will be reported regardless of whether they are related to the use of drugs or surgery in the study. It is the responsibility of the investigators to notify independent ethics committees or governmental regulatory authorities related to adverse events.

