### Secondary Objectives

- To compare the PFS of patients in the treatment of D2 gastrectomy plus liver radiofrequency plus postoperative chemotherapy to those treated with chemotherapy alone

- To explore a comparison of the total incidence of complications of D2 gastrectomy plus liver radiofrequency plus postoperative chemotherapy to those of chemotherapy alone

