### Terminating Study Criteria

The terminating study criteria are as follows:

- Patients are unable to undergo surgery for various reasons after enrollment (reasons need to be recorded);- The researchers consider that the patients are not suitable to continue the clinical trial (the reason for withdrawal should be recorded);- Patients with serious complications or unbearable adverse reactions;- Patients request that the trial be terminated;- Patients violated the treatment principles (violation of injection and discharge standards, disobedience to the study chemotherapy arrangement, etc.)

We will terminate the study for individual patients once they meet the termination criteria and their data will not be included in the final analysis. Other patients who meet the criteria for admission but do not meet the criteria for termination will continue to participate in our study.

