### Treatment Protocols

All eligible patients will be randomly divided into a test group or a control group according to a 1:1 distribution ratio. The test group will receive D2 gastrectomy plus liver radiofrequency plus postoperative chemotherapy. In the test group, only open surgery is allowed. The control group will receive chemotherapy alone. The chemotherapy regimens of the two groups are the same (11), S-1 plus cisplatin. S-1 will be given orally 80-120 mg/m² per day for the first 3 weeks of every 5-week cycle. The dose of S-1 will be given according to the patients’ body surface area (less than 1.25 m², 80 mg; 1.25–1.5 m², 100 mg; and greater than 1.5 m², 120 mg). Patients will receive cisplatin 60 mg/m² on Day 8 of every 5-week cycle *via* intravenous infusion. **Table 1** shows the treatments applied in this study. **Table 2** shows the medication and usage in this experiment. Because all enrolled patients are tested for the molecular profile of the tumors, such as HER2, PDL1, MSI and MMR expression, follow up treatment protocols could be adjusted according to the patients’ molecular profile, such as trastuzumab or immunotherapeutic antibody. Accordingly, in the statistical analysis of data, different patients also require conduct subgroup hierarchical analysis according to the molecular detection results of tumors to reduce data error.

**Table 1 T1:** The treatments applied in this study.

	gastrectomy (total gastrectomy, distal or proximal gastrectomy plus D2 lymph node dissection)	liver radiofrequency	chemotherapy (S-1 + cisplatin)
test group	√	√	√
control group	—	—	√

**Table 2 T2:** The medication and usage in this experiment.

Chemotherapy drugs	dose	Timing of the drugs (a total of 35 days/cycle)			
		Day 1-7/cycle	Day 8/cycle	Day 9-21/cycle	Day 22-35/cycle
S-1	80-120 mg/m² (oral)	√	√	√	—
cisplatin	60 mg/m² (intravenous infusion)	—	√	—	—

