To verify the comparison of the efficacy of D2 gastrectomy plus liver radiofrequency plus postoperative chemotherapy versus chemotherapy alone for patients with GCLM, we designed a superiority study with a superiority margin of 5% (α= 0.05, β= 0.20, 80% power). With a standard error of 0.05 and a confidence interval of 80%, a sample size of 178 is necessary. To minimize sampling error and account for the rate of loss to follow-up for various reasons, we determined the sample size to be 200 participants. Standard descriptive statistics will be used to analyze qualitative and quantitative variables such as relative and absolute frequencies, frequency tables, means, medians, standard deviations, ranges, and quartiles. A 95% confidence level will be considered appropriate for analysis. Descriptive statistics will also be used to describe the most relevant clinical parameter measurements. Analysis of categorical variables will be performed by two-sample t tests or Fisher’s exact test. If there is no significant difference in the response rate to D2 gastrectomy plus liver radiofrequency plus postoperative chemotherapy versus chemotherapy alone, then the result will be negative, that is, the difference is not related to whether to apply the treatment strategy of D2 gastrectomy plus liver radiofrequency plus postoperative chemotherapy for patients with GCLM; otherwise, there is a relationship.

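### The termination rule, followed as written, removes patients with serious complications from the only named safety endpoint

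*Protocol article*

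**What the plan says.** The Secondary Objectives section sets one safety comparison between the arms: "To explore a comparison of the total incidence of complications of D2 gastrectomy plus liver radiofrequency plus postoperative chemotherapy to those of chemotherapy alone". Study Endpoints names this total complication rate beside PFS as a secondary endpoint and defines its content: "The total complications will include postoperative and chemotherapy complications". Postoperative complications have a 30-day window and Clavien-Dindo grading, and 30-day postoperative mortality is defined.

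Terminating Study Criteria includes "Patients with serious complications or unbearable adverse reactions" among the reasons for ending a patient's participation. It then says that the study ends for individual patients "once they meet the termination criteria and their data will not be included in the final analysis".

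The adverse-event text under Study Endpoints says: "All serious adverse events will be reported regardless of whether they are related to the use of drugs or surgery in the study". It goes on to the investigators' duty to notify ethics committees or authorities. Under Treatment Protocols, "The chemotherapy regimens of the two groups are the same", and only the test group has gastrectomy and liver radiofrequency.

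**The concern.** The event that the endpoint should count is also the event that takes the patient out of the analysis. A patient with a serious anastomotic leak meets the termination criterion because of that leak, so the leak drops out of the complication rate. No section makes an exception for safety data.

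The loss is not the same in the two arms. Serious chemotherapy toxicity can remove patients from either arm, but serious procedural complications can remove them only from the test arm. The trial adds open D2 gastrectomy and liver ablation to chemotherapy in patients with a poor prognosis. Readers will set the complication result against any survival gain, and a rate computed without its serious cases understates what they need to weigh.

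**Working it through.** The plan states no expected complication rate, so it has no figure to reproduce here. The rates below are assumptions. The arm size of 100 is from the abstract.

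**Serious procedural complications in the test arm.** Suppose k of 100 patients have one and a share f of them is removed. The analysed set then shows k(1−f)/(100−kf).

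| True count | All removed (f = 1) | Half removed (f = 0.5) | All randomised, exact 95% CI |
|---|---|---|---|
| 5 of 100 | 0% | 2.5/97.5 = 2.6% | 1.6% to 11.3% |
| 10 of 100 | 0% | 5/95 = 5.3% | 4.9% to 17.6% |
| 15 of 100 | 0% | 7.5/92.5 = 8.1% | 8.6% to 23.5% |

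This step does not depend on the chemotherapy event rate or on whether patients or events are counted in the pooled rate.

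**The pooled rate in each arm.** Notation and assumptions:

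- c = chemotherapy complication rate, equal in both arms; t = its serious part
- q = procedural complication rate, test arm only; s = its serious part
- chemotherapy and procedural events independent; each patient counts once; all serious cases removed

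Before removal: test = 1−(1−c)(1−q), control = c, difference = (1−c)q.

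After removal: with P = 1−(1−s)(1−t), test = [1−(1−c)(1−q)−P]/(1−P) and control = (c−t)/(1−t).

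Example with c = 50%, q = 30%, s = 10%, t = 10%:

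- Test before: 1−0.50×0.70 = 65.0%.
- P = 1−0.90×0.90 = 0.19, so 81 are analysed. Test after: (0.65−0.19)/0.81 = 56.8%.
- Control before: 50.0%. After: (0.50−0.10)/0.90 = 44.4%, with 90 analysed.

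An arm's rate falls whenever any of its patients are removed for a serious event. At t = 0 the control rate does not move.

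**The difference between the arms.** After removal it is [(1−c)/(1−t)]×[(q−s)/(1−s)]. Its ratio to the difference before removal is (q−s)/[q(1−s)(1−t)], which does not involve c. All three cases have q = 30%.

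| c | s | t | Difference before | Difference after |
|---|---|---|---|---|
| 30% | 10% | 0% | 21.0 points | 15.6 points |
| 50% | 10% | 10% | 15.0 points | 12.3 points |
| 30% | 5% | 20% | 21.0 points | 23.0 points |

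With q = 30% the difference grows rather than shrinks once t passes about 5% (s = 2%), 12% (s = 5%) or 26% (s = 10%). The direction is therefore not fixed.

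**Pooling, taken separately.** With no removal, q = 30% shows as (1−c)q: 21.0 points at c = 30%, 15.0 at c = 50% and 8.6 at c = 71.4%. The last value is the 5 of 7 quoted in the sample size section for any adverse event in an earlier trial (exact 95% CI 29% to 96%), so it is one imprecise point in a range.

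**The case against.** The strongest reply is that procedural harm is recorded anyway. Complications are graded, 30-day mortality is defined, serious adverse events must be fully recorded and reported, and a day-14 visit looks for postoperative complications. That stands as far as data collection goes. It does not settle who enters the comparison, because the reporting duty does not put terminated patients back into the final analysis. A reader might call the two rules a contradiction. The text does not go that far: reporting an event and omitting the patient from an analysis can coexist, and the article does not say which rule governs this endpoint.

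A reader might also infer that pooling surgical and chemotherapy complications is itself an error. The documents do not support this. The total rate answers the question set in the Secondary Objectives, which compares whole strategies. The postoperative component is defined and graded separately, and nothing says that only the pooled figure will be shown. The dilution depends on an unknown chemotherapy rate and on each patient counting once, which the article does not fix.

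Nor does the text say that a non-significant complication rate will be taken as no added harm. The sentence under Sample Size Estimate and Statistical Analysis, "then the result will be negative, that is, the difference is not related to whether to apply the treatment strategy", concerns response rate.

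Finally, the exclusion is general and also reaches OS and PFS. That is true, but the safety effect is distinct: here the outcome itself triggers the removal.

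**Conclusion.** The point holds for the termination rule. As written, the total complication rate loses its most serious cases, and the procedural part of that loss falls only on the test arm. Serious procedural complications would read as 0% if all such patients are removed. If half are removed, true rates of 5%, 10% and 15% would read as 2.6%, 5.3% and 8.1%. These are illustrations, since the protocol gives no rates and does not say what share of cases would be terminated.

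The pooled rate is understated in each arm that loses serious cases. A reader might infer that the rule always hides the added harm, but the difference between arms can move either way, so only distortion can be claimed. Those pooled calculations also rest on independence, an equal chemotherapy rate in both arms and counting each patient once. The problem should be corrected. It affects the reported safety result, and no stopping rule uses this rate.

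**What to change.** Add a sentence to Terminating Study Criteria: the exclusion from the final analysis does not apply to complications, adverse events or deaths. State under Study Endpoints that the total complication rate is analysed in all randomised patients, including those terminated.

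Optional, and not a correction of an error: beside the pooled rate, show procedural complications by Clavien-Dindo grade and 30-day postoperative mortality. Both are already provided for. This would let readers see the surgical contribution where shared chemotherapy side effects might dilute it.

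The cost is small: wording, plus keeping terminated patients' safety data. The test arm's safety result may look less favourable than under the current rule.

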### Clinical Data

Clinical data from the patients will be obtained by medical staff and recorded on an online electronic platform (http://www.medresman.org.cn) and in the CRF table. The samples will be coded, and the patients’ identity will be known only by the attending physician. The clinical data will include the following: general patient information, past medical history, past surgical history, laboratory examination results, imaging results, surgery details, PFS and OS. The timing and processing of the above recorded contents will be reflected in the CRF table, and the laboratory examinations will mainly assess preoperative and postoperative routine blood, liver function, tumor markers, and inflammatory indicators. The prognosis of GC with liver metastasis (GCLM) was very poor, with a 5-year survival rate of <10% (17). Patients will be assessed at least monthly from baseline for adverse events *via* verbal interview, physical examination, and blood tests, including a complete blood cell count and assessments of liver and renal function, until disease progression. Abdominal CT and measurements of tumor markers, such as carcinoembryonic antigen, carbohydrate antigen 199, carbohydrate antigen 125, carbohydrate antigen 153 and alpha fetoprotein, were done every 3 months.

A detailed description of the above data is shown in the CRF table. **Table 3** shows the test and data acquisition schedule for this experiment.

**Table 3 T3:** The test and data acquisition schedule for this experiment.

Stage	Pre-operation	Intra-operation	Postoperation					Unplanned follow-up
Follow up period	14-1 days		0-12 month	13-24 month	25-36 month	37-48 month	49-60 month	
Baseline data collected	√	—	—	—	—	—	—	—
Inclusion and exclusion	√	—	—	—	—	—	—	—
Sign informed consent	√	—	—	—	—	—	—	—
Group determination	√	—	—	—	—	—	—	—
Fill in the basic information	√	—	—	—	—	—	—	—
Physical examination	√	—	√	√	√	√	√	—
Imaging examination	√	—	√	√	√	√	√	if necessary
Laboratory examination	√	—	√	√	√	√	√	—
Operation information	—	√	—	—	—	—	—	—
Postoperative pathology	—	√	—	—	—	—	—	if necessary
Safety observation	√	—	√	√	√	√	√	if necessary
Record adverse events	√	—	√	√	√	√	√	if necessary
Other works	√	√	√	√	√	√	√	if necessary

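### As worded, the complication and postoperative mortality measures leave out events confined to the operation, and Table 3 contradicts the adverse-event windows in the text

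*Protocol article*

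**What the plan says.** The total complication rate is a secondary endpoint. Study Endpoints gives its composition: "The total complications will include postoperative and chemotherapy complications". The surgical part has a time window: "Postoperative complications were defined as events occurring within 30 days after the procedure". The chemotherapy part consists of drug side effects. Mortality has the same starting point: "Postoperative mortality was defined as all-cause death occurring within 30 days after the procedure". No intraoperative category is named.

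Table 3 (Clinical Data) has an Intra-operation column. In the row "Record adverse events" and in the safety-observation row, that column holds a dash. Both rows are ticked before the operation and in every postoperative year, and marked as needed for unplanned visits. The column is otherwise in use: operation information, pathology and other works are ticked there.

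The adverse-event paragraph of Study Endpoints says something different. Adverse events "will be considered from the date participants sign informed consent until 5 years after the end of treatment in this study". For serious events: "The investigators will keep a full record of serious adverse events from the start of the surgery to the end of the study". The same paragraph opens with a narrower definition: "Adverse events are adverse medical events that occur after surgical and medical treatment in patients in clinical trials".

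Under Treatment Protocols and Table 1, only the test group receives gastrectomy and liver radiofrequency.

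**The concern.** The comparison of complication rates is meant to show what adding surgery and ablation costs the patient. If the measure starts only once the procedure is over, harm confined to the procedure itself has no place in it. Bleeding controlled in theatre and an organ injury repaired at once are examples. Only the test arm has that period for gastrectomy and radiofrequency, so an omission can lower only that arm's figures.

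Separately, a site cannot follow both Table 3 and the adverse-event paragraph for the time in theatre. Sites that resolve the conflict differently would collect different data.

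**Working it through.** The plan has no figure of its own on this point, so the check is mainly a comparison of the stated time windows.

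| Place | What is counted or recorded | Start | Covers the operation? |
|---|---|---|---|
| Study Endpoints, complication definition | Postoperative complications | After the procedure, to 30 days | No, read literally |
| Study Endpoints, complication definition | Chemotherapy complications | Drug side effects | No |
| Study Endpoints, mortality definition | All-cause death | After the procedure, to 30 days | No, read literally |
| Study Endpoints, adverse-event definition | Adverse events | After treatment | No, read literally |
| Study Endpoints, adverse-event window | Adverse events | Consent | Yes |
| Study Endpoints, serious adverse events | Serious adverse events | Start of surgery | Yes |
| Table 3 | Safety observation, adverse-event recording | Dash at Intra-operation | No |
| Table 3 | Operation information | Ticked at Intra-operation | Yes |

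Two things follow.

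1. **Recording.** Table 3 conflicts with the consent-based and surgery-based windows. The adverse-event paragraph is also inconsistent within itself, because its definition starts after treatment and its window starts at consent.
2. **Endpoint.** Letting the wider windows prevail for recording does not close the gap. An intraoperative event on the serious adverse event record still belongs to neither part of the total complication rate as defined.

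**Size.** No intraoperative event rate is given, so what follows is illustration only. Let b be the share of test-arm patients counted anyway for another complication. Let r be the assumed share with an intraoperative event among the remaining patients. Then

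understatement = (1 − b) × r.

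For b, I take the two adverse-event rates printed in Sample Size Estimate and Statistical Analysis, 60% and 81.8%. The article prints 60% for gastrectomy plus chemotherapy, but the 9 of 11 it reports for that group is 81.8%. Both therefore serve as candidate base rates, with the caution that they are adverse-event rates from a trial of gastrectomy without radiofrequency.

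| Assumed r | b = 60% | b = 81.8% |
|---|---|---|
| 2% | 0.40 × 2 = 0.8 points | 0.182 × 2 = 0.4 points |
| 5% | 0.40 × 5 = 2.0 points | 0.182 × 5 = 0.9 points |
| 10% | 0.40 × 10 = 4.0 points | 0.182 × 10 = 1.8 points |

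The control-arm rate does not change in any row, because that arm has neither procedure.

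**The case against.** The strongest reply is that little is lost.

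- **Recording.** From the dashes in Table 3 a reader might infer that adverse-event recording is switched off during the operation. The documents do not support that. The text window runs through the operation, serious events are kept from the start of surgery, and operation information is collected in theatre. Table 3 is a summary, and the article refers to a case report form that is not shown. This stands: the recording part is a contradiction, not a decision to stop recording.
- **Visibility.** A reader might also infer that those overseeing safety would never see such events. For serious ones this is wrong, since all serious adverse events are to be reported. A death on the table also counts in overall survival, the primary endpoint. Non-serious events are less certain.
- **Width of the gap.** Injury in theatre that shows itself within 30 days is still counted. The list of other complications is open-ended and names bleeding, abscess and pancreatic fistula. For surgical site infection the wording is broader still: "SSI refers to the infection that occurs in the incision, deep organ or cavity during the perioperative period". This stands too: what is left out is events that begin and end in theatre, plus table deaths in the 30-day mortality figure.
- **Asymmetry.** Eligibility calls for diagnostic exploration in all patients, so surgical risk as such is not unique to the test arm. The one-sidedness concerns gastrectomy and radiofrequency.
- **Size.** It is tempting to say that 2, 5 or 10 patients in 100 with an intraoperative event mean an understatement of 2, 5 or 10 points. That is true only if none of them has any other counted complication, so it restates the assumption.

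One can also argue that a category labelled postoperative is coherent on its own terms. It is. But it is then one of only two parts of a rate called total, and the total omits the operation.

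**Conclusion.** The point holds as a gap in a secondary endpoint together with an internal contradiction. Followed literally, the definitions in Study Endpoints exclude purely intraoperative events of gastrectomy and radiofrequency from the total complication rate, and deaths on the table from postoperative mortality. Table 3 contradicts the adverse-event and serious adverse event windows. The direction is certain: any omission favours the test arm.

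The size cannot be derived from the documents. It is probably small, because many patients will have another counted complication. The illustration of 0.4 to 4.0 points rests on assumed event rates of 2% to 10% among patients otherwise free of counted complications, and on base rates of 60% to 81.8%. The primary comparison of overall survival is not affected by these definitions.

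**What to change.** - **Table 3:** tick the Intra-operation cells for safety observation and adverse-event recording, so that the schedule agrees with the windows in Study Endpoints. Bring the sentence that defines adverse events as occurring after treatment into line at the same time.
- **Study Endpoints:** count surgical complications and mortality from the start of the procedure (gastrectomy and radiofrequency) through day 30, and state that intraoperative events enter the total complication rate. The start then agrees with the one already set for serious adverse events.
- **Terminating Study Criteria:** this section lists serious complications as a ground for ending a patient's participation and removes such patients' data from the final analysis. State that this removal of data does not apply to the complication endpoint. Otherwise a patient with a serious intraoperative event could still be dropped, and the change would not take full effect.

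The cost is two table cells, one definition and one sentence on the data rule. Operative information is already collected and no visit is added. The downside is a slightly higher reported complication rate in the test arm.

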### Follow-up

When patients are discharged from the hospital, the first follow-up is to be performed on the 14th day after surgery. The patients will be given physical examination, imaging examination and laboratory examination to determine the postoperative complications of the patients during the follow-up period. The next chemotherapy plan will be formulated for the patients according to the above results. Physical examination and laboratory examination will be performed at least monthly on all enrolled patients. Imaging examinations will be performed every three months. The patients will be followed up by researchers every month to every 3 months. In addition to the above, the complications of chemotherapy will be examined. Recurrence, metastasis, death, and dates of patients will be recorded. The contents of each follow-up will be collated and combined. The follow-up contents will be recorded in **Table 3**.

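### The total complication rate counts surgical events only to day 30 but chemotherapy side effects with no stated end, so late gastrectomy or ablation complications are left out of the between-arm comparison

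*Protocol article*

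**What the plan says.** Secondary Objectives sets a between-arm aim: "To explore a comparison of the total incidence of complications" under the two strategies. Study Endpoints turns this into an endpoint ("The secondary endpoints PFS and total complication rate") and gives its parts: "The total complications will include postoperative and chemotherapy complications".

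The two parts are then defined differently:

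- Surgical part: "Postoperative complications were defined as events occurring within 30 days after the procedure", graded by Clavien-Dindo, with a list of surgical and perioperative examples.
- Drug part: "Chemotherapy complications refer to the side effects of chemotherapy, such as ototoxicity and nephrotoxicity". No time limit is attached.

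Under Treatment Protocols, gastrectomy and liver radiofrequency belong to the test arm. "The control group will receive chemotherapy alone".

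The adverse-event text in Study Endpoints is wider. It covers events related or unrelated to treatment, from consent to five years past the end of treatment. It asks investigators to judge the relation to drugs and to surgery, and it keeps serious events on record to study end.

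**The concern.** A total that is compared between arms should give every relevant event the same chance of being counted in each arm. Here the component that both arms share has no stated end, while the component specific to gastrectomy and ablation stops at day 30. An abdominal abscess or intestinal obstruction caused by the operation and first seen on day 38, or an abscess at an ablation site on day 45, is too late for the surgical part and is not a drug side effect. It adds nothing to the total.

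This endpoint carries the harm side of a comparison between surgery plus ablation and no surgery. A rule that can only remove test-arm events makes the test strategy look safer than it is.

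**Working it through.** The plan gives no figure for this endpoint, so there is none to reproduce. The check has two parts.

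**1. Which events the rule counts**

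| Event | Surgical part (to day 30) | Drug part (by cause) | In the total? | Arms that can have it |
|---|---|---|---|---|
| Gastrectomy or ablation complication, day 20 | yes | no | yes | test only |
| Gastrectomy or ablation complication first seen on day 38 or 45 | no | no | **no** | test only |
| Chemotherapy side effect, any day | not needed | yes | yes | both |

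Only the second row is lost, and only the test arm can contribute to it.

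**2. Size of the loss**

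Inputs:

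- pc, chance of a chemotherapy complication, equal in both arms: 5/7 = 71.4%, the count that Sample Size Estimate and Statistical Analysis cites for chemotherapy patients with liver metastases; 50% as an alternative. The 5/7 is an all-adverse-event count in seven patients, so it is only a placeholder.
- s, chance of a surgical complication by day 30: 20-30% (assumption).
- L, chance of a surgical or ablation complication after day 30: 3-10% (assumption).
- The three are taken as independent (assumption).

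Formulas:

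- Control rate = pc
- Test rate as defined = 1 − (1 − pc)(1 − s), so the reported excess = (1 − pc)s
- Test rate with late events = 1 − (1 − pc)(1 − s)(1 − L)
- Understatement = (1 − pc)(1 − s)L

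| pc | s | Reported excess | Excess with late events, L = 3% / 5% / 10% | Understatement (points) |
|---|---|---|---|---|
| 5/7 | 20% | 5.7 | 6.4 / 6.9 / 8.0 | 0.7 / 1.1 / 2.3 |
| 5/7 | 30% | 8.6 | 9.2 / 9.6 / 10.6 | 0.6 / 1.0 / 2.0 |
| 50% | 20% | 10.0 | 11.2 / 12.0 / 14.0 | 1.2 / 2.0 / 4.0 |
| 50% | 30% | 15.0 | 16.1 / 16.7 / 18.5 | 1.1 / 1.7 / 3.5 |

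Example: pc = 5/7, s = 20%, L = 10% gives 0.2857 × 0.80 × 0.10 = 0.0229, or 2.3 points.

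As a share of the true excess, the factor (1 − pc) cancels and leaves (1 − s)L / [1 − (1 − s)(1 − L)]. This runs from 0.021/0.321 = 7% (s = 30%, L = 3%) to 0.08/0.28 = 29% (s = 20%, L = 10%).

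For scale: with 100 patients per arm and rates of 71.4% and 77.1%, the standard error of the difference is √(0.714 × 0.286/100 + 0.771 × 0.229/100) = 0.062. The 95% half-width is about 12 points.

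**The case against.** **The 30-day cut is a stated and objective choice.** The same section uses it for postoperative mortality, and it avoids years of open-label judgement about whether an obstruction or abscess comes from surgery or from tumour. This stands as a reason to keep the 30-day figure. It does not justify using that figure as one half of a total compared with an arm whose events have no stated cut-off.

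**The effect is small and rests on assumed rates.** This stands. The objective is also worded as exploratory. But the bias has a known direction, and more patients would not remove it.

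**The chemotherapy side is not truly unlimited.** Clinical Data describes at least monthly adverse-event assessment until progression, and adverse-event coverage ends five years after treatment. Correct, so the point is only that the endpoint definition states no limit. Either horizon would usually run well past day 30.

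Three stronger readings are tempting, and the document does not support them:

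- *Late surgical events are lost to the trial.* They are not. The adverse-event text covers them. They are missing from this endpoint only.
- *Early chemotherapy toxicity is counted as surgical.* A reader might infer this because the 30-day definition speaks only of events, and because singling out "patients delayed postoperative systemic radiotherapy and/or chemotherapy after 4 weeks of surgery" implies that chemotherapy can start inside the 30 days. But chemotherapy complications are defined by cause, and nephrotoxicity is named among them. At most, a rule for unclear cases is absent. Misfiling would change the component rates and the grading scale, not whether a patient counts in the total.
- *Follow-up contradicts the 30-day cut* where it says examinations serve "to determine the postoperative complications of the patients during the follow-up period". That sentence comes directly after the day-14 visit and before the planning of chemotherapy. Its natural meaning is the day-14 visit, which lies within the 30 days.

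**Conclusion.** The concern holds in a limited form. Read as written, the total complication rate omits gastrectomy and ablation complications that first occur after day 30. Only the test arm can have these, so the comparison understates test-arm harm. With late complications in 3-10% of patients, 30-day surgical complications in 20-30%, chemotherapy complications in 50-71% and independence, the understatement is about 0.6 to 4 points. None of the surgical rates comes from the documents; a different late rate would change the size but not the direction. This is a modest flaw in a secondary endpoint. It does not touch overall survival, and it is worth correcting because the correction is cheap.

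**What to change.** In Study Endpoints, separate the between-arm endpoint from the surgical-quality figure:

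1. For the between-arm comparison, count complications in both arms over one common window that starts at randomisation, using the adverse events and causality assessment already planned. State the length of the window, and assess both arms in the same way to its end.
2. Keep the 30-day Clavien-Dindo postoperative rate as a separately labelled descriptive figure for the test arm.
3. Where chemotherapy starts within 30 days of surgery, assign events to components by attributed cause. This affects the component rates only.

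**Cost:** a change of wording, with no new type of data. The reported test-arm rate may rise slightly. Attribution involves some judgement by unblinded clinicians; counting all complications in the common window whatever their cause would keep that judgement out of the total and confine it to the component rates.
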